### Randomization, blinding, and allocation

Following baseline assessment, participants will be randomly allocated to either the experimental or the control group in a 1:1 ratio. The allocation sequence will be generated in R using the *blockrand* package by an independent researcher not involved in participant recruitment, intervention delivery or outcome assessment, with a random seed kept confidential until recruitment is complete.

Block randomization will be used, with permuted blocks of variable size (4, 8, and 12) and 1:1 allocation within each block, without stratification given the homogeneity of the target population in age and academic context. Using variable block sizes that are not disclosed to enrolling staff preserves allocation concealment by preventing prediction of forthcoming assignments, while ensuring balanced group sizes throughout recruitment and minimizing selection bias.

Recruiting and enrolling staff remain masked to the allocation sequence and to the (variable) block sizes throughout the trial. As a post-hoc verification of the absence of allocation selection bias, a Berger–Exner test will be applied to check for any association between the allocation sequence and baseline prognostic characteristics.

Due to the nature of the psychoeducational intervention, blinding of participants and intervention providers (facilitators) will not be feasible. Outcome data will be collected using self-administered standardized questionnaires, minimizing assessor-related bias.

Researchers involved in data management and statistical analysis will remain blinded to group allocation until the primary analyses are completed. Data will be coded using anonymized group identifiers to ensure concealment during analysis.

This approach ensures appropriate separation between sequence generation, allocation concealment, and blinding procedures, in accordance with established guidelines for randomized controlled trials.

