Assessments will be conducted at three time points: baseline, immediate post-intervention, and six-month follow-up. To ensure both adherence and intervention fidelity, facilitators will receive prior specific training and follow a structured session guide. Fidelity to the protocol will be monitored by the research team using standardized checklists completed after each workshop. Additionally, a set of retention strategies will be implemented to minimize attrition and missing data, including periodic email reminders and advance notifications of session schedules. Attendance will be systematically monitored throughout the intervention, and participants will be reminded of the importance of continuous participation from the outset to ensure data completeness across all assessment points.

Table 2 presents the standardized pedagogical structure applied in each workshop session, comprising six sequential phases that combine initial welcome, experiential activation, psychoeducational input, group-based activities, individual reflection, and a brief closing synthesis.

**Table 2 pone.0355374.t002:** Standard pedagogical structure of each workshop session.

Session phase	Duration	Description
Welcome and psychological climate	5 min	Facilitators welcome participants, present the objectives of the session, and establish a supportive and non-evaluative group climate
Experiential activation	10 min	Short reflective or experiential activity designed to activate participants’ previous experiences and beliefs related to the workshop topic
Psychoeducational content	15 min	Brief evidence-based explanation of the key concept addressed in the workshop (e.g., motivational regulation, body functionality, social support)
Experiential group activity	20 min	Interactive activities conducted in pairs or small groups allowing participants to apply the concepts through discussion, reflection, or body-awareness exercises
Personal reflection and transfer	5 min	Individual reflection on how the workshop content relates to participants’ own behaviors and experiences
Closing and synthesis	5 min	Summary of key ideas and encouragement to apply the concepts in everyday life

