### Wait-list control condition

Participants assigned to the control group will remain on the wait-list during the intervention and follow-up periods and will not receive any specific intervention. To ensure intervention equity, they will be offered access to the full program upon completion of the T2 assessment.

Participants in both groups will be allowed to continue their usual activities and access external health-related services (e.g., psychological support, personal training, or dietary counseling) throughout the study period. To monitor potential sources of contamination, participants will be asked to report any engagement in such services during the study.

These data will be recorded and considered in the interpretation of the findings. If deemed necessary, additional sensitivity analyses will be conducted to explore the potential impact of external interventions on the study outcomes.

All protocol deviations, including non-adherence to the intervention or engagement in external programs, will be documented and reported following established guidelines for randomized controlled trials.

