An appropriate covariance structure (e.g., unstructured or alternative based on model fit indices) will be specified to account for within-participant correlations across repeated measurements. The primary endpoint will be the between-group difference at six-month follow-up, while effects at post-intervention will be considered secondary analyses. Least-squares mean differences between groups will be estimated from the model, along with corresponding 95% confidence intervals and p-values. This likelihood-based approach uses all available observed data without imputing missing values and provides valid inferences under the missing at random (MAR) assumption. Secondary outcomes, including satisfaction and frustration of basic psychological needs, physical activity levels, positive body image, and risk of eating disorders, will be analyzed using equivalent MMRM approaches. In cases where parametric assumptions are violated, robust mixed-effects models and bootstrapping procedures will be applied to obtain reliable parameter estimates. Exploratory analyses of the six BREQ‑3 subscales will follow the same mixed‑effects modelling approach. In addition, mediation will be tested with a half-longitudinal model [34]: group is the independent variable, the change in autonomous motivation (BREQ-3 RAI) from T0 to T1 is the mediator, and the changes in physical activity (IPAQ-SF), positive body image (BAS-2), and eating disorder risk (EAT-26) from T1 to T2 are the outcomes. The primary specification is a single-level structural equation model (lavaan) with bias-corrected bootstrap confidence intervals for the indirect effect; a multilevel SEM that accounts for the partially nested delivery subgroups is reported as a sensitivity analysis. Full detail is given in the SAP (see Supporting information S3 File). Statistical significance will be set at p < .05. Effect sizes will be calculated to facilitate interpretation of the magnitude of effects. Ninety-five percent confidence intervals will be reported for all relevant estimates.

To enhance transparency and reproducibility, a complete Statistical Analysis Plan (SAP, v2.0), structured following the template by [35], is provided as supplementary material (S3 File).

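### The analyst blind is guaranteed only through the primary analyses, so the data-dependent choices left for the secondary and mediation analyses could be made with the arms known

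*Protocol article*

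**What the plan says.** Under Randomization, blinding, and allocation, the article states that "blinding of participants and intervention providers (facilitators) will not be feasible" and that "Outcome data will be collected using self-administered standardized questionnaires, minimizing assessor-related bias". It then sets the analyst blind: "Researchers involved in data management and statistical analysis will remain blinded to group allocation until the primary analyses are completed". Coded group labels are the only stated means of keeping it. The same section says "Recruiting and enrolling staff remain masked to the allocation sequence and to the (variable) block sizes throughout the trial"; that is allocation concealment and does not bear on how outcomes are reported or analysed.

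Under Statistical analysis, the primary endpoint is the between-group difference in the Relative Autonomy Index at T2, and T1 effects are secondary. The other outcomes are to be analysed by equivalent mixed models. The covariance structure is left to be chosen, possibly on fit indices. On departures from assumptions: "In cases where parametric assumptions are violated, robust mixed-effects models and bootstrapping procedures will be applied to obtain reliable parameter estimates". On mediation, the single-level model is primary and "a multilevel SEM that accounts for the partially nested delivery subgroups is reported as a sensitivity analysis".

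Under Wait-list control condition: "If deemed necessary, additional sensitivity analyses will be conducted to explore the potential impact of external interventions on the study outcomes". Under Experimental intervention: "Attendance will be systematically monitored throughout the intervention", and each participant stays in one delivery subgroup of at most 15.

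**The concern.** Participants and facilitators know the allocation and every outcome is self-reported, so the analyst blind is the only blind in the trial once allocation has been made. The Discussion credits it with reducing bias. As worded, its protection is assured only up to the end of the primary analyses.

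The article's remaining judgements mostly come after that point, or may do so. Whoever decides that a secondary outcome departs enough from its assumptions to need a robust model, or that an external-service analysis is worth running, could already know which arm is which and how the primary comparison came out. At stake is the credibility of the results for hypotheses H2 to H6: need satisfaction, physical activity, body appreciation, eating disorder risk and mediation. The primary endpoint is not directly affected.

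**Working it through.** No sample size, power or significance figure bears on this point. The check is a comparison of the article's own statements.

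1. **When the blind ends.** It ends at completion of the primary analyses (Randomization, blinding, and allocation).

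2. **What counts as primary.** Statistical analysis names one primary endpoint, the T2 difference in the Relative Autonomy Index, and classes the T1 effect on the same outcome as secondary. The natural reading is that the blind need not outlast the primary model.

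3. **What is left to judge, and when.**
   - *Robust or bootstrap models.* The condition is a violation of parametric assumptions. Whether it is met has to be judged from the data, outcome by outcome. For secondary outcomes this can fall after the blind ends.
   - *Covariance structure.* It is open for the primary model and, through the equivalent models, for each secondary outcome. The primary choice falls inside the blind; the secondary choices may not.
   - *External-service analyses.* These are run if judged necessary, and the article gives no trigger. The decision may come late.

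4. **Whether coded labels are enough while the blind lasts.** Controls receive no sessions before T2 (Wait-list control condition), so attendance and delivery subgroup exist only for the experimental arm. The target is 196 participants at 1:1, so 196 / 2 = 98 per arm. With at most 15 per subgroup, 98 / 15 = 6.5, so at least 7 subgroups. If either variable were merged with the coded data before T2 is complete or before the primary model is run, one code would carry entries and the other blanks, and the arms would be plain. That would also expose the covariance choice in the primary model.

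5. **Whether the main analyses need those variables.** They do not. The primary model uses group, time, their interaction and the baseline value; the secondary models are equivalent; the primary mediation model is single-level. Attendance serves the per-protocol analysis and subgroup serves the multilevel mediation model, both of them sensitivity analyses. The variables can therefore be added late without delaying any main result.

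**The case against.** The strongest reply is that the plan already has the better safeguard. Statistical analysis says all analyses are specified before database lock and cites a complete statistical analysis plan in S3 File, which may fix the triggers, the per-protocol definition and the order of unblinding. This stands, and it limits the exposure to whatever is still open after lock. It does not remove the point, because a rule that depends on a condition still needs someone to judge whether the condition is met.

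A second reply is that primary analyses, in the plural, is undefined. Intention-to-treat is called the primary approach and mediation has a primary specification, so the blind may be meant to reach further. This is possible, but the wording does not secure it.

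A third is that the external-service analysis is an added sensitivity analysis and replaces no estimate. That is correct, and it lowers the stakes of that choice.

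Three stronger readings are tempting and are not supported:
- *That the later choices will be made with the arms known.* The article shows only that they could be.
- *That the blinded team already holds the one-arm variables.* No section says who keeps attendance or subgroup data or when they are merged. The risk is conditional on an early merge.
- *That early unblinding inflates type I error by a calculable amount.* Reporting the smaller of two two-sided p-values does raise the error rate, but an analyst who sees only coded arms can do that as well. Such a figure would not measure the harm of lifting the blind, and a longer blind would not remove it.

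**Conclusion.** The point holds in a limited form. The article guarantees analyst blinding only for the primary analyses, while data-dependent choices remain for the secondary, subscale and mediation analyses. These could be made with the arms and the primary result known. This is a minor weakness in a stated strength of the design. It contradicts nothing in the protocol and does not invalidate the primary comparison.

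The conclusion rests on two assumptions: that primary analyses means the analysis of the primary endpoint, and that some of these choices are still open after database lock. If the statistical analysis plan closes them or sets a later unblinding point, what remains is to bring the protocol sentence into line with it. No numerical size is given, because nothing in the documents allows one.

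**What to change.** Revise the blinding sentence under Randomization, blinding, and allocation so that data managers and analysts stay blinded until both of these are done:
- the covariance-structure, robust-model and external-service decisions have been recorded;
- the primary, secondary, subscale and single-level mediation models have been run.

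Add that attendance and delivery-subgroup data are kept out of the analysis file until then, and are merged only for the per-protocol and multilevel sensitivity analyses.

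The cost is a change of wording, one file held apart, and a slightly later unblinding of the analysts. By the article's own timeline recruitment had not begun at submission, so the change can be made before any data exist. Under Ethics and dissemination, important modifications go to the ethics committee and the registry; the sponsor should decide whether this one qualifies.

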### Procedure and intervention

The intervention is grounded in Self-Determination Theory [10,11] and is described following TIDieR recommendations to ensure clarity and reproducibility. It adopts an autonomy-supportive approach, integrating strategies aimed at satisfying the basic psychological needs of autonomy, competence, and relatedness. This approach has consistently been associated with increases in autonomous motivation and improvements in health-related behaviors in educational and physical activity contexts [14,15,23].

After providing written informed consent, participants will complete the baseline assessment using self-administered digital questionnaires designed to evaluate motivation toward physical activity and secondary psychological and behavioral study variables. Upon completion of the initial assessment, participants will be randomly assigned in a 1:1 ratio to either the experimental group or the control group.

#### Experimental intervention.

Participants assigned to the experimental group will take part in a face-to-face psychoeducational program consisting of six 60-minute group workshops, conducted in small groups of up to 15 participants. Each participant remains in the same delivery subgroup across the six sessions. This format facilitates social interaction and the creation of a need-supportive climate, factors identified as relevant in interventions based on Self-Determination Theory (SDT). Sessions are facilitated by trained professionals with experience in exercise science and psychonutrition, who receive standardized training prior to intervention delivery to ensure consistency across groups. Facilitators complete standardized training covering SDT principles, functionality‑based body image strategies, session structure, and fidelity procedures. The intervention includes structured presentation slides, participant worksheets, guided experiential activities, and reflective exercises. Detailed intervention materials are available from the authors upon reasonable request. Minor contextual adaptations (e.g., examples or wording adjustments) may be made, but core intervention components remain unchanged. The intervention will be delivered following a standardized manual based on established SDT techniques, including autonomy support, structure, and involvement [13,14], as summarized in Table 1.

**Table 1 pone.0355374.t001:** Structure, objectives, and Basic Psychological Needs-Supportive Strategies targeted in the intervention workshops.

Workshop	Primary focus	Need-Supportive Strategies (SDT-based)	Basic Psychological Needs targeted
1	Awareness of motivational quality toward PA	Providing a meaningful rationale: explaining the “why” behind PA engagement.	Autonomy
2	Personal values and autonomously chosen goals	Autonomy support: promoting the internalization of PA goals based on personal interests.	Autonomy & Competence
3	Perceived competence and flexible planning	Structure: providing clear guidance, mastery-oriented feedback, and skill-building for PA.	Autonomy & Competence
4	Positive body image from a functionality-oriented perspective	Acknowledging perspectives: validating participants’ feelings and fostering intrinsic values.	Autonomy & Relatedness
5	Social support and supportive relational climate	Involvement: fostering a warm, supportive, and non-judgmental climate for PA.	Relatedness
6	Maintenance of change and management of difficulties	Action planning: identifying future supports and strategies for managing PA challenges.	Competence

**Note:** SDT = Self-Determination Theory; PA = Physical Activity.

Each workshop combines brief psychoeducational content with interactive, experiential activities designed to promote reflection, personal meaning, and supportive peer interaction. Activities are structured to support autonomy (choice provision, validation of personal perspectives), competence (mastery‑oriented tasks, individualized progress‑focused feedback), and relatedness (collaborative group climate). This multicomponent structure aligns with evidence identifying these elements as key mechanisms for enhancing autonomous motivation in health‑behavior interventions [14,15].

A distinctive feature of the program is the incorporation of functionality‑oriented body image content. This approach shifts attention from appearance to bodily capabilities and has been associated with improvements in body appreciation and reductions in ED‑related risk factors among young women [16–18]. Integrating functionality appreciation within an SDT‑based framework is expected to reduce appearance‑based exercise motives and reinforce autonomous regulation, helping prevent maladaptive patterns such as compulsive or guilt‑driven exercise [8,9].

Across the six workshops (Table 1), participants will progressively work on: (1) awareness of motivational quality toward exercise; (2) identification of personal values and self‑endorsed goals; (3) competence development through flexible planning; (4) functionality‑focused body appreciation; (5) strengthening social support; and (6) maintenance of behavior change and management of challenges. Fidelity will be monitored using session checklists completed after each workshop. This design integrates components targeting motivational and psychosocial processes identified as relevant factors in the prevention and reduction of eating disorder symptomatology and other health-related behaviors [19,24]. Participants in both groups will be asked to maintain their usual lifestyle habits throughout the study period, and no restrictions will be imposed on concurrent physical activity or health-related behaviors.

Assessments will be conducted at three time points: baseline, immediate post-intervention, and six-month follow-up. To ensure both adherence and intervention fidelity, facilitators will receive prior specific training and follow a structured session guide. Fidelity to the protocol will be monitored by the research team using standardized checklists completed after each workshop. Additionally, a set of retention strategies will be implemented to minimize attrition and missing data, including periodic email reminders and advance notifications of session schedules. Attendance will be systematically monitored throughout the intervention, and participants will be reminded of the importance of continuous participation from the outset to ensure data completeness across all assessment points.

Table 2 presents the standardized pedagogical structure applied in each workshop session, comprising six sequential phases that combine initial welcome, experiential activation, psychoeducational input, group-based activities, individual reflection, and a brief closing synthesis.

**Table 2 pone.0355374.t002:** Standard pedagogical structure of each workshop session.

Session phase	Duration	Description
Welcome and psychological climate	5 min	Facilitators welcome participants, present the objectives of the session, and establish a supportive and non-evaluative group climate
Experiential activation	10 min	Short reflective or experiential activity designed to activate participants’ previous experiences and beliefs related to the workshop topic
Psychoeducational content	15 min	Brief evidence-based explanation of the key concept addressed in the workshop (e.g., motivational regulation, body functionality, social support)
Experiential group activity	20 min	Interactive activities conducted in pairs or small groups allowing participants to apply the concepts through discussion, reflection, or body-awareness exercises
Personal reflection and transfer	5 min	Individual reflection on how the workshop content relates to participants’ own behaviors and experiences
Closing and synthesis	5 min	Summary of key ideas and encouragement to apply the concepts in everyday life

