To address these gaps, the present study describes a randomized controlled trial evaluating a psychoeducational intervention designed to enhance autonomous motivation for PA and promote positive body image among female Health Sciences students. Grounded in SDT and enriched with functionality-focused components, the intervention targets theoretically central mechanisms, basic psychological need satisfaction and autonomous regulation, to support sustainable PA engagement and reduce vulnerability to ED-related risk factors. By intervening in a high-risk developmental period and focusing on future health professionals, this trial holds potential not only for improving individual well-being but also for fostering autonomy-supportive communication styles that may influence future clinical practice.

Based on the theoretical framework, existing empirical evidence, and the identified gaps in the literature, the present study proposes the following hypotheses:

*Primary hypothesis*

H1. The intervention will significantly increase autonomous PA motivation (BREQ-3; Relative Autonomy Index) at post-intervention (T1) and follow-up (T2).

*Secondary hypotheses*

H2. Participants will report higher basic psychological need satisfaction (autonomy, competence, and relatedness; BPNSFS) at post-intervention (T1) and follow-up (T2).H3. PA levels (IPAQ-SF) will increase significantly at T1 and T2.H4. Participants will show significant improvements in positive body image (BAS-2).H5. Eating disorder risk (EAT-26) will be significantly reduced.

*Mediation hypothesis (key mechanism)*

H6. Changes in autonomous motivation will mediate the intervention’s effect on PA levels and health-related psychological outcomes.

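### The request to both arms to keep usual lifestyle habits conflicts, for the experimental arm, with the physical-activity hypothesis (H3), the activity path of H6 and the workshop content

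*Protocol article*

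**What the plan says.** Under Experimental intervention, the article gives one instruction to both arms for the whole study: "Participants in both groups will be asked to maintain their usual lifestyle habits throughout the study period". The sentence continues: "and no restrictions will be imposed on concurrent physical activity or health-related behaviors".

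The hypotheses in the Introduction expect behaviour to change. H3 reads "PA levels (IPAQ-SF) will increase significantly at T1 and T2", and H6 reads "Changes in autonomous motivation will mediate the intervention’s effect on PA levels and health-related psychological outcomes". Under Statistical analysis, the mediator is the T0 to T1 change in the Relative Autonomy Index (RAI), and "the changes in physical activity (IPAQ-SF), positive body image (BAS-2), and eating disorder risk (EAT-26) from T1 to T2 are the outcomes".

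The programme is built to produce that change. In Table 1 the strategy for workshop 6 is "Action planning: identifying future supports and strategies for managing PA challenges". The text after the table gives the aim of that workshop as "maintenance of behavior change and management of challenges". Table 2 closes every session with "Summary of key ideas and encouragement to apply the concepts in everyday life".

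The section on the wait-list control condition is worded differently. It permits both groups to carry on as usual and to use outside services, and asks them to report such use.

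**The concern.** Physical activity is a lifestyle habit, and it is what the IPAQ-SF measures. A woman in the experimental arm who takes the request at face value until T2 cannot also show the rise that H3 predicts. She attends six sessions that help her plan and sustain activity, and is asked at the same time to leave her habits as they are.

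What is at stake is the reading of a secondary outcome and of one mediation path. If H3 comes out null, part of the explanation could be that participants did as they were asked. The article describes monitoring of attendance, session fidelity and use of outside services. It describes no record of who held their habits constant because of the request, so the two explanations could not be separated afterwards. The analysis cannot undo an instruction already given.

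**Working it through.** The article gives no figure for this point, so there is nothing to reproduce. The check sets the statements side by side and then asks which analyses the request can reach.

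**Step 1. What the experimental arm is told or expected to do**

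| Place in the article | Content | Direction for physical activity |
|---|---|---|
| Experimental intervention, first half of the sentence | Asked to keep usual habits, both groups, whole study | No change |
| Same sentence, second half | Activity not restricted | Change permitted |
| Wait-list control condition | Both groups may carry on as usual and use outside services | Change permitted |
| Table 1 and the workshop list | Goals, flexible planning, skill-building, maintaining changed behaviour | Change supported |
| Table 2, closing phase | Encouraged to use the content in daily life | Change encouraged |
| H3 | Activity rises at T1 and T2 | Change predicted |

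The first row stands alone against the others. It is an active request. The second and third rows are permissions, and a permission does not withdraw a request.

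**Step 2. Which analyses it can reach**

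- *Primary outcome* (RAI at six months): a motivation score, not a habit. Not directly affected.
- *H3* (IPAQ-SF at T1 and T2): directly affected.
- *H6, group to mediator* (RAI change, T0 to T1): not directly affected.
- *H6, mediator to IPAQ-SF change* (T1 to T2): directly affected, because the request covers this whole interval and discourages turning motivation into behaviour.
- *H6, mediator to BAS-2 change*: body appreciation is not a habit. Not directly affected.
- *H6, mediator to EAT-26 change*: not directly affected; at most indirectly, through eating habits.

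So one secondary outcome and one of the three mediation outcomes are exposed.

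**Step 3. Direction and size**

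Let D be the effect on activity that the programme would have without the request. Let q be the share of the experimental arm that follows it. Assume that a participant who follows it shows no programme-induced change in activity. The contrast is then

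(1 − q) × D.

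At q = 0 it equals D; at q = 1 it is 0. The direction is toward no difference for any q above 0. The article gives neither q nor a value of D for the IPAQ-SF, so the range runs from no attenuation to complete attenuation, and nothing in the text narrows it.

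**The case against.** The strongest reply is that the sentence must be read to its end. The second half expressly leaves physical activity free, the wait-list section only permits usual activities, and the deviations named there are non-adherence to the programme and engagement in external programmes. Increased activity is not named. Six sessions of activity support outweigh one clause that looks like standard wording about life outside the programme. The participant-facing text is not shown, so how the request will be put to participants is unknown.

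Much of this stands. A reader might infer that the plan forbids experimental participants to become more active; read whole, the sentence does not say that. The reply does not remove the conflict, because the request is still made, to both arms and for the whole study, and nothing withdraws it.

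Other strong inferences also lack support:

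- *A null on H3 would be uninterpretable.* The randomised contrast would still estimate the effect of the programme as delivered, request included. A null would be harder to explain, not meaningless.
- *The control arm's natural change is suppressed.* Nothing in the article shows this. Usual-habit wording is compatible with a wait-list, and controls may use outside services.
- *Power for physical activity collapses.* Take 196 × 0.80 / 2 ≈ 78 per arm and assume a baseline correlation of 0.5. With d = 0.30 the noncentrality is 0.30 / √0.75 × √(78/2) ≈ 2.16 and power about 0.58. If half the arm complies, d = 0.15, noncentrality is about 1.08 and power about 0.19. The arithmetic is sound, but the compliance share, the correlation and the IPAQ-SF effect are all assumed. The article's d of 0.20 to 0.30 belongs to simulations of the primary RAI contrast.

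**Conclusion.** The inconsistency is real and of moderate weight. The article asks the experimental arm to keep its habits while predicting, teaching and encouraging a change in one of them. To the extent the request is followed, the IPAQ-SF contrast for H3 and the physical-activity path of H6 are biased toward no difference. The amount cannot be estimated from the document.

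This rests on two assumptions: that participants will receive the request roughly as the article words it, and that some in the experimental arm will take physical activity to be among their lifestyle habits. If neither holds, the point reduces to unclear wording.

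A reader might extend the criticism to the whole mediation analysis or to the trial's main conclusion. The text does not support that: the primary RAI comparison and the BAS-2 and EAT-26 paths are not directly touched.

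**What to change.** Before recruitment opens, reconcile the sentence under Experimental intervention with H3 and H6, with Tables 1 and 2, and with the wait-list section, so that it is clear what each arm is asked to do. Remove the request to keep usual habits for behaviours that are trial outcomes, physical activity first among them. Keep the permissive wording of the wait-list section and its reporting of outside services; these already serve to monitor co-interventions. Check that the participant information and facilitator materials carry the same wording.

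The cost is small: an edit to one sentence, the matching line in participant materials if it appears there, and a submission to the ethics committee under the article's own amendment procedure. No change to sample size, assessments or analysis is needed. Recruitment is expected to start in October 2026 and had not begun when the article was submitted. Once participants have been given the request, the edit can no longer repair the comparison for them.
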